Poor adherence to clinical guidelines is not unique to Spain. In the year 2007, a similar problem was identified in the United Kingdom, ultimately leading to the development of a program entitled “IAPT” designed to promote the treatment of EDs in PC with CBT in accordance with the NICE recommendations (NICE, 2011). That initiative has been very successful, resulting in substantially improved treatment outcomes while simultaneously reducing costs (particularly due to decreased drug prescriptions) compared to the usual PC treatment (Radhakrishnan et al., 2013). Indeed, given the success of the IAPT program with EDs, the program has been extended for use in children and in patients with chronic physical conditions (Gyani et al., 2013). Due to the considerable savings of the CBT approach versus drug-based therapies, one recent study estimated that even if the number of patients treated with CBT in the PC setting doubled (from 500,000 to 1 million per year), the net cost would likely be zero if patients with common mental disorders (anxiety and depression) and those with comorbid chronic physical conditions receive CBT (Layard and Clark, 2015).

In Spain, a randomized controlled clinical trial [the Psychology in Primary Care (PsicAP) study] is currently in progress to compare evidence-based psychological techniques [such as transdiagnostic (TD)-CBT] to treatment-as-usual (TAU) (Cano-Vindel et al., 2016) in patients with EDs. Given this context, the present work describes the design of a study being conducted as part of the PsicAP clinical trial (sub-study 2). The aim of this sub-study is to assess and compare the costs associated with psychological and pharmacological treatment approaches for mental disorders in the PC setting in Spain. This study will assess the relationship between cost-effectiveness and cost-utility of these two different treatment approaches. We hypothesize that the costs of switching from TAU to a group-based TD-CBT approach will be justified by the expected additional clinical and social benefits (a superiority trial).

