### Interventions

#### Experimental Group

The treatment program is included within a collaborative protocol of a stepped-care model of treatment, as recommended by the NICE (2011) guidelines. The first step involves group TD-CBT based on a treatment manual [Cordero-Andrés et al., 2017; González-Blanch et al., 2017; Cano-Vindel (Unpublished)]. The characteristics of this treatment have been described previously by Cano-Vindel (2011). EDs are believed to originate from a dual process of dysfunctional emotional learning over time that involves both cognitive (increasing use of cognitive distortions) and associative (classical conditioning in some significant emotional events) learning. Although this dysfunctional learning tends to lead to symptom chronicity and the development of new, comorbid disorders, the process is considered to be reversible. Moreover, both types of functional relearning (i.e., cognitive and associative) can be achieved with cognitive-behavioral techniques such as cognitive restructuring and behavioral exposure. A transdiagnostic approach (Newby et al., 2015), which involves simplification and economy of resources by applying similar therapeutic procedures to different EDs, will be used in this group intervention. However, the unique characteristics of the cases in each group will be taken into consideration.

Patients in the experimental group will be divided into subgroups of approximately eight patients each and will be treated by clinical psychologists specifically trained for this program. The intervention will include seven sessions (1.5 h/session) delivered over a 24-week period. The contents include the following: psychoeducation, cognitive restructuring, relaxation, behavioral training, and relapse prevention.

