#### Control Group Intervention

All patients in the control group will receive standard treatment (TAU) from their GP according to the usual criteria. In most cases, this will involve pharmacological treatment.

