#### Description of Cost Analysis

Direct costs of health care will be estimated by adding the costs derived from medication use (antidepressants, hypnotics, sedatives, and anxiolytics), medical tests, use of health-related services, and staffing costs. The cost of medications will be calculated by determining the price per milligram (mg) during the study period according to the Vademecum International (Vidal, 2014), including value-added tax. Total costs of medications will be calculated by multiplying the price per mg by the daily dose (mg) and the number of days of drug treatment.

The main source of unit cost data related to public medical tests and use of health services will be obtained from the fee information published by the Official Government Journal of the Autonomous Community of Madrid (2013). Indirect costs will be calculated according to the number of days on sick leave multiplied by the minimum daily wage in Spain for 2015 (€21.62). Finally, total costs will be calculated by summing the total direct and indirect costs. The unit costs will be expressed in Euros (€) based on 2015 prices.

Currently, there is no reference fee for the TD-CBT intervention that will be used with the experimental group. The estimated cost of a consultation with a public sector GP in Spain is €39 (not including complementary tests). Given that salaries for psychologists in Spain are similar to those of GPs, we will use this amount (€39) to calculate the cost of the TD-CBT intervention (i.e., €39 multiplied by the number of assessment and treatment sessions, €39 × 9 = €351). Since the GP consultation fees are understood to include the cost of office space, we will not add any additional costs for office rent to the cost of the therapy. Accordingly, the total cost of the evaluation and psychological intervention (nine sessions) per person is estimated at €43.87 (€351/8).

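### The fixed TD-CBT cost of €43.87 per patient leaves out, without saying why, the programme-specific training that only the TD-CBT arm requires; the omission favours TD-CBT by an unknown and possibly small amount

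*Protocol article*

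**What the plan says.** The Introduction states the hypothesis of the sub-study as being that "the costs of switching from TAU to a group-based TD-CBT approach will be justified by the expected additional clinical and social benefits". The Discussion repeats it.

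Under Experimental Group, subgroups of about eight patients "will be treated by clinical psychologists specifically trained for this program", working from a treatment manual. On duration: "The intervention will include seven sessions (1.5 h/session) delivered over a 24-week period". Under Control Group Intervention: "All patients in the control group will receive standard treatment (TAU) from their GP according to the usual criteria". No added training is described for that arm.

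The Description of Cost Analysis notes that TD-CBT has no reference fee and borrows one: "The estimated cost of a consultation with a public sector GP in Spain is €39 (not including complementary tests"). The borrowing is justified by pay: "Given that salaries for psychologists in Spain are similar to those of GPs, we will use this amount (€39"). Office rent is not added, because the GP fee is taken to include it. The result is that the total cost of the evaluation and "psychological intervention (nine sessions) per person is estimated at €43.87 (€351/8").

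Training does not appear in that formula, in the list of direct-cost components in the same section, or in the resource list under Economic Assessment. The Sensitivity Analysis section announces an analysis of robustness without naming its inputs.

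**The concern.** Training psychologists for a new manualised programme uses resources in one arm only, because the comparator is care that already exists. The two reasons given for the €39 fee, similar salaries and included office space, do not extend to training. The section also discusses what should or should not be added to the price, and explains the exclusion of rent, but it is silent on training.

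The TD-CBT price enters the difference in mean costs, which is the numerator of both the cost-effectiveness and the cost-utility ratio. Leaving out a positive cost in one arm moves that difference in one direction, towards TD-CBT. Bootstrapping will not reveal this, since it resamples patients whose TD-CBT cost already lacks the item. At stake is whether a finding that switching is justified would also hold once the cost of preparing staff is counted.

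**Working it through.** **Inputs from the protocol.** Fee €39 per session, nine assessment and treatment sessions, group size 8 (Description of Cost Analysis); treatment sessions of 1.5 h (Experimental Group); 150 patients per arm (Sample Size); nine Madrid centres plus two added later (Protocol Amendments 2 and 5).

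**Step 1. Reproduce the stated price.** 39 × 9 = 351; 351 / 8 = 43.875, printed as €43.87. The three factors account for the whole figure, so the training term is €0.

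**Step 2. Direction.** Let *t* be the training cost per TD-CBT patient. Adding it raises mean TD-CBT cost, and so the incremental cost, by exactly *t*. If TD-CBT is the more effective arm, each ratio rises by *t* divided by the difference in effect or in QALYs. For any *t* > 0 the current rule favours TD-CBT.

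**Step 3. Size, under assumptions.** The protocol gives no training hours, number of psychologists trained or training cost. I assume 8 to 40 hours per psychologist. Time is priced from €26 per hour (39 / 1.5, the rate implied by the treatment sessions) to €39 per hour. Trainer fees are excluded. The number trained is also unknown: the Blinding section speaks of one psychologist for the TD-CBT group, while the Experimental Group section uses the plural. I therefore show one, nine and eleven, the last two being one per Madrid centre.

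*t* = psychologists × hours × hourly rate / patients sharing the cost

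| Trained | Patients sharing the cost | Low (8 h, €26) | High (40 h, €39) | Relative to €43.875 |
|---|---|---|---|---|
| 1 | 150 | 1 × 8 × 26 / 150 = €1.39 | 1 × 40 × 39 / 150 = €10.40 | 3% to 24% |
| 9 | 150 | 9 × 8 × 26 / 150 = €12.48 | 9 × 40 × 39 / 150 = €93.60 | 28% to 213% |
| 11 | 150 | 11 × 8 × 26 / 150 = €15.25 | 11 × 40 × 39 / 150 = €114.40 | 35% to 261% |
| any number | 500 per psychologist | 8 × 26 / 500 = €0.42 | 40 × 39 / 500 = €3.12 | 1% to 7% |

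**Step 4. Scale.** The ratios use total direct plus indirect costs, not the TD-CBT price alone. The protocol values a day of sick leave at €21.62. On that scale €3.12 is 0.14 of a day (3.12 / 21.62), €10.40 is 0.48 of a day (10.40 / 21.62) and €114.40 is 5.3 days (114.40 / 21.62). The protocol gives no expected cost difference, so whether any of these amounts would change a conclusion cannot be computed.

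**The case against.** The strongest reply has four parts.

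*The article is condensed.* Amendment 4 refers to a section on therapist training that this article does not contain, and the direct costs include an undefined staffing item. Training might be costed in a document not shown. This stands as a reason for caution about what the full protocol says. It does not change the article's own rule, which fixes the TD-CBT total numerically and calls it the total cost.

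*The wording of the hypothesis.* A reader might infer that "the costs of switching from TAU to a group-based TD-CBT approach will be justified" commits the trial to counting transition costs, so that the analysis contradicts its own hypothesis. The protocol does not support that. The phrase can equally mean ordinary incremental cost: the Cost-Effectiveness Analysis section defines the ratio by the difference in mean costs, and the Discussion moves from the hypothesis to the cost of treating these disorders. The ambiguity is a reason to say which cost is meant, not proof of a contradiction.

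*The convention.* Leaving one-off training out of a steady-state costing is defensible. This stands, so nothing here requires training in the base case.

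*The size.* The upper figures need eleven psychologists, 40 hours each, €39 per hour and no use of the training beyond the trial. None of these comes from the protocol. This also stands: a range from 1% to 261% of the price shows mainly that the size is unknown.

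**Conclusion.** The point holds in a limited form. The stated TD-CBT cost contains no training, training specific to the programme is required in that arm only, and no reason is given for leaving it out. The direction is certain for any positive training cost.

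The size is not known. Under the assumptions above it is about €1 to €10 per patient with one psychologist trained, and €15 to €114 with eleven, when all of it falls on the 150 TD-CBT patients. It is about €0.4 to €3 when spread over 500 patients per psychologist.

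Two stronger inferences are tempting and go beyond the documents. One is that the ratios are materially wrong or that the conclusion would reverse; without training records or an expected cost difference this cannot be shown. The other is that therapist supervision is a further missing cost; the protocol does not mention supervision, so the point rests on training alone. This is an inexpensive improvement in transparency and robustness, not a fault that invalidates the analysis.

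**What to change.** In the Description of Cost Analysis, keep €43.87 as the base case, subject to any other correction to it, and label it as a running cost that excludes training, with the reason.

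Under Sensitivity Analysis, add a training cost per treated patient: training hours × hourly staff cost, summed over the psychologists trained and divided by the patients treated. Use two bounds: zero, and all training charged to the TD-CBT patients in the trial. Report whether the cost-effectiveness and cost-utility conclusions hold at both. State the hours, the number of psychologists trained and the hourly rate used.

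The cost is a little extra costing work and a somewhat less favourable upper-bound cost for TD-CBT. The sponsor must supply the training hours and the number trained; no new patient data are needed.

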#### Control Group Intervention

All patients in the control group will receive standard treatment (TAU) from their GP according to the usual criteria. In most cases, this will involve pharmacological treatment.

### Clinical Evaluation

Patients will be assessed at baseline, immediately after treatment finalization, and at 6 and 12 months post-treatment.

### Instruments

The PHQ is a screening test derived from self-reported tests of the PRIME-MD system (Spitzer et al., 1999), an evaluation system for mental disorders in the PC setting, validated in Spain by Diez-Quevedo et al. (2001). This system contains a number of self-report instruments that can detect the presence of depressive, anxiety, and somatoform disorders (Kroenke et al., 2010).

The PHQ-9 (Kroenke et al., 2001) is an instrument specifically designed to screen for depression; patients are asked to rate each of the 9 DSM-IV criteria. Only symptoms occurring during the 2 weeks prior to the evaluation are considered. Items are rated on a four-point Likert scale from 0 to 3, as follows: 0 (never), 1 (several days), 2 (more than half of the days), and 3 (most days). For a diagnosis of MDD, the algorithm requires a score of 2 or 3 on at least one of the first two symptoms, and must score 2 or 3 on at least 5 of the 9 items (the 9th item-suicide attempts-also counts with a score of 1). A score ≥ 10 is considered the best cut-off point for screening, presenting a sensitivity of 0.88 and specificity of 0.88. McMillan et al. (2010) found that therapeutic success could be assessed with the PHQ-9 as follows: patients with a post-treatment score below the cut-off level (≤9) who experienced a one standard deviation (five point) decrease from pre-treatment scores could be considered in remission, while scores ranging from 10 to 14 indicated minor depression, dysthymia or moderate major depression while scores from 15 to 19 indicated moderately severe major depression, and scores from 20 to 27 indicating severe major depression. Another item (item 10) has been added to evaluate the degree of dysfunction (McMillan et al., 2010). In the Spanish PC setting, PHQ-9 has shown to be a highly satisfactory tool that can be used for screening MDD (Muñoz-Navarro et al., 2017a,c).

The GAD-7 (Spitzer et al., 2006) is used to rate seven common anxiety symptoms presenting during the prior 2 weeks. This instrument can be used not only as a screening test for GAD, but also for other anxiety disorders. The maximum score is 21. Anxiety is classified as mild (≤5 points), moderate (6–14 points), or severe (≥15). The validated Spanish version developed by García-Campayo et al. (2012) was used instead of the original version of the PHQ (Diez-Quevedo et al., 2001). Using a cut-off score of 10 points, the GAD-7 has a sensitivity of 89% and specificity of 82% for GAD. A computerized version of the GAD-7 has been shown to be an excellent screening tool for detecting general anxiety disorder in Spanish PC settings (Muñoz-Navarro et al., 2017b).

The PHQ also contains the DSM-IV symptoms of panic disorder, PHQ-PD (Wittkampf et al., 2011). Patients who answer “yes” to the first four questions and present ≥ 4 symptoms are considered to have a probable diagnosis of panic disorder. Its psychometric properties have been studied with Spanish patients from PC centers (Muñoz-Navarro et al., 2016).

The PHQ-13 includes 13 somatic symptoms, with a maximum score of 26. To detect a probable diagnosis of somatization disorder, at least 3 of the first 13 symptoms must receive the maximum score (two points), and there can be no biological explanation for the somatic disorder. A more recent version—the PHQ-15 (Kroenke et al., 2002), which includes two additional items—has been developed; in the validation study, 88% of the patients who met these criteria had a somatoform disorder; however, psychometric values were lower in later studies (sensitivity, 0.78; specificity, 0.71 (van Ravesteijn et al., 2009; Kroenke et al., 2010).

The Sheehan Disability Rating Scale (Sheehan et al., 1996) is a self-administered test that subjectively evaluates the degree of disability or dysfunction across three life domains—work, social, and family life—using three scales. Two additional items also assess the degree of stress in the last week and the perceived level of social support. The first four items are scored on a 10-point scale ranging from 0 (unimpaired) to 10 (maximum disability). Scores ranging from 1–3, 4–6, and 7–9 indicate, respectively, mild, moderate, or high disability. The fifth item (perceived social support) utilizes the same type of scale, but this is expressed as a percentage, ranging from 0% (non-existent support) to 100% (perfect support).

### Economic Assessment

In this study, our aim was to compare the association between cost-effectiveness and cost-utility of the two treatments. The economic evaluation will be conducted by recording variables (see below) obtained from patient medical records and patient interviews.

To quantify direct costs, the following variables (only related to EDs) will be registered and assessed: number of patient consultations with psychologists and/or psychiatrists; number of patient visits to the PC centers (GP, nurse, or social worker); number of patient visits to public or private hospitals; number of visits to clinics/physicians associated with private health insurance companies; number of road traffic, workplace, or domestic accidents; number of hospitalizations and emergency room visits; medications used (name of drug, daily dose, and duration of treatment); consultations with other therapists (i.e., podiatrists, physiotherapists, and dieticians). Diagnostic tests requested by the GP and/or specialists to assess physical symptoms secondary to the emotional disorder(s) will be included. Indirect costs will include all days off from work. If a replacement worker is needed, then this will be registered as an indirect cost as well.

All the variables will be collected for the following time points: 3 months before study inclusion; at baseline; immediate post-treatment; and at 6 and 12 months post-treatment.

After providing written informed consent, the participants will be registered in the treating center. Pre- and post-treatment assessments are to be carried out using computerized self-reported screening tests. All pretreatment assessments will be performed at the treating PC center after scheduling an appointment with the clinical psychologist. A computer with Internet access is used to collect data. All data are stored on a general virtual website (surveymonkey.com). At all post-treatment follow-up assessments, the same instruments will be completed in person at the treating center.

#### Retention

If necessary, we will send the participant a link by email to enable the patient to complete the computerized measures at home. Patients are contacted by phone to encourage completion of the questionnaires. Patients who discontinue or drop out of treatment will still be invited to complete the post-treatment follow-up assessments, particularly the first post-treatment assessment.

### Main Outcomes

The main outcomes are the clinical symptoms assessed by the PHQ: depression, anxiety, panic, and somatic symptoms, as well as economical variables and EuroQol 5D outcomes in terms of QALYs.

### Secondary Outcomes

Measures of disability will be included in the secondary outcomes. The following socio-demographic variables will be registered and analyzed: sex; marital status (married, divorced, widow/widower, separated, single, cohabitation); age; education level (none, elementary education, secondary education, university education, post-graduate degree); work status (part-time employee, full-time employee, temporary incapacity for work or permanently disabled, unemployed); and household income level (<€12,000; €12,001 - €24,000; €24,001 - €36,000; >€36,000).

### Statistical Analysis

#### Analysis of Clinical Effectiveness

This study will be conducted on an intention-to-treat basis. Both groups will be compared to verify that there are no significant between-group differences at baseline. For comparisons, the ANOVA method will be used for continuous variables and the Chi-square test for categorical variables. Subsequently, a repeated measurement of ANOVA, including all variables over time, will be performed to assess whether missing values respond to a random or non-random pattern. If the missing values are greater than 5% the Expectation Maximization (EM) will be used as a data imputation method, as recommended by the literature (Schlomer et al., 2010).

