#### Assignment of Interventions

##### Allocation

After informed consent is obtained, participants are randomly assigned to either the treatment or control group by a researcher, according to a blind research design, using a computer-generated allocation sequence, thus assuring comparable groups on main outcomes. Each group will include approximately 8–10 patients randomly allocated to the experimental (TD-CBT) or control group (TAU). Subjects will receive the allocation information via email from a graduate student trainee affiliated with the project. The email will also provide login details and website information for the allocated intervention.

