#### Cost-Effectiveness Analysis

The cost-effectiveness analysis will be carried out by calculating the incremental cost-effectiveness ratios (ICER), defined as the difference in mean costs divided by the increase in effectiveness of the various therapeutic alternatives.

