#### Cost-Utility Analysis

Cost-utility analysis is a method of economic evaluation based on preferences or utilities rated by individuals; in other words, the value that an individual assigns to their health status. Thus, the economic evaluation depends on the social perspective of the individual, in which patients express preferences about their health. The EuroQoL-5D Questionnaire (EQ-5D – Spanish version) will be used for the cost-utility analysis. This is a generic QOL instrument consisting of five domains, as follows: mobility; anxiety/depression; pain/discomfort; daily activities; and self-care. These five domains are coded into five severity levels, as follows: no problems; slight problems; moderate problems; severe problems; extreme problems. In this way, 3125 distinct health states can be established. Health states enable us to obtain a population-based preference score per country (the EQ-5D index). The assigned values range from 0 (death) to 1 (perfect health). In addition, this index includes a VAS similar to a thermometer, which measures health from 0 (worst imaginable health state) to 100 (best imaginable health state) (Rabin et al., 2015).

Through the EQ-5D health questionnaire, we will calculate utility as QALYs using the Spanish fees described above.

Using these data, we will calculate the incremental cost-utility ratios, defined as the difference in mean costs divided by the difference in mean QALYS. Given that the duration of this study is only 12 months, neither costs nor outcomes are subject to discount. To obtain more precise cost-utility ratios, these ratios will be calculated by means of the bootstrapping method (a resampling method), which involves creating a large number of samples with replacement from the original sample data, thus allowing for a distribution that better resembles the actual distribution of the population from which the original data was drawn. In this way, the study will generate 1000 random samples which will be used to define the confidence intervals for the cost-utility ratios.

Missing-data analysis will be computed using Student’s *t*-test and chi-square tests. Variables included in the analysis will be severity level, gender, and age; this will allow us to ascertain whether unexpected missing data due to participant dropout are related to chance or not.

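### Baseline significance tests cannot verify comparability, and the cost and QALY differences are defined without a baseline term although the covariates are available

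*Protocol article*

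**What the plan says.** In the Protocol article, Analysis of Clinical Effectiveness, the first analytic step is: "Both groups will be compared to verify that there are no significant between-group differences at baseline". The method is given as: "the ANOVA method will be used for continuous variables and the Chi-square test for categorical variables". No consequence is attached to a significant result. The Allocation section describes the random sequence as "thus assuring comparable groups on main outcomes".

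The economic contrasts are defined in two places. Under Cost-Effectiveness Analysis the ratio is "defined as the difference in mean costs divided by the increase in effectiveness of the various therapeutic alternatives". Under Cost-Utility Analysis it is "defined as the difference in mean costs divided by the difference in mean QALYS". For uncertainty, patients are resampled with replacement and "the study will generate 1000 random samples which will be used to define the confidence intervals for the cost-utility ratios". None of these sections mentions baseline utility, baseline cost or a regression step.

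The covariates are available. Economic Assessment says resource use is collected for "3 months before study inclusion; at baseline; immediate post-treatment; and at 6 and 12 months post-treatment". The Abstract and Clinical Evaluation place an assessment at baseline, and the Abstract lists the EuroQol 5D-5L among the instruments. The article does not list EQ-5D visit by visit; I take the general schedule to cover it.

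**The concern.** A baseline test in a randomised trial tests a null hypothesis that is true by design if allocation was carried out properly. It can neither confirm comparability nor identify the imbalances that matter. What matters is how strongly a covariate predicts outcome and how far it happens to differ, not whether p falls below 0.05.

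The better use of baseline data is adjustment. QALYs need it most: under the usual area-under-the-curve calculation, baseline utility is part of the QALY itself, so a chance gap at entry passes directly into the QALY difference. Costs are similar in kind, since prior resource use usually predicts later resource use. Costs and QALYs are among the main outcomes and are the reason for this sub-study. The article also adopts 150 per group after calculating 176, so precision that costs nothing is worth having.

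**Working it through.** The article has no figure of its own on this point to reproduce, and it gives no SD, correlation or expected QALY gain. Inputs marked (assumed) are mine.

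**Inputs**
- 150 per group: Sample Size.
- Treatment over 24 weeks: Experimental Group. Follow-up to 12 months post-treatment: Clinical Evaluation. Cost-Utility Analysis instead gives the study duration as 12 months, so both horizons are shown.
- Utility SD 0.20, range 0.15 to 0.25 (assumed).
- Half of a baseline utility gap persists at later times (assumed).
- QALY by trapezoidal area under the curve (assumed).

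**1. What the baseline test lets through.** In SD units the standard error of a baseline difference is sqrt(2/150) = 0.115. A difference up to 1.96 × 0.1155 = 0.226 SD is declared non-significant. Conversely, under proper randomisation, 6 to 10 independent tests at 5% (number and independence assumed) give at least one significant result with probability 1 − 0.95^6 = 26% to 1 − 0.95^10 = 40%. Neither outcome says anything about whether allocation worked.

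**2. Effect of a chance gap on the QALY difference.** Regression adjustment replaces the raw difference by

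adjusted difference = raw QALY difference − b × (baseline utility difference),

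where b is the slope of QALY on baseline utility. The raw difference therefore carries b × gap. At SD 0.20 the one-standard-error gap is 0.20 × 0.1155 = 0.0231.

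- *12 months, half persisting throughout:* b = 0.5 × 1.0 = 0.5.
- *24 weeks plus 12 months, half persisting throughout:* the horizon is 24/52 + 1 = 1.46 years, so b = 0.5 × 1.46 = 0.73.
- *Same horizon, baseline at its full trapezoid weight:* the direct weight is (24/52)/2 = 0.231 years and the remainder is 1.231 years, so b = 0.231 + 0.5 × 1.231 = 0.846.

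| Assumed SD | SE of gap | 12 months | 1.46 years, half throughout | 1.46 years, full baseline weight |
|---|---|---|---|---|
| 0.15 | 0.0173 | 0.009 | 0.013 | 0.015 |
| 0.20 | 0.0231 | 0.012 | 0.017 | 0.020 |
| 0.25 | 0.0289 | 0.014 | 0.021 | 0.024 |

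The last three columns are QALYs per one standard error of chance imbalance.

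**3. Precision.** Linear adjustment multiplies the variance of a mean difference by about 1 − ρ², where ρ is the correlation of the outcome (QALY or cost) with its baseline covariate. For assumed ρ of 0.3, 0.5 and 0.7 the factor is 0.91, 0.75 and 0.51. That is equivalent to 150/0.91 = 165, 150/0.75 = 200 and 150/0.51 = 294 per arm unadjusted. No cost SD is given, so the effect on the cost difference cannot be put in euros.

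**The case against.** The strongest reply is that the ratio definitions are the textbook ones. A ratio of regression-adjusted mean differences would also satisfy them, a bootstrap can carry a regression, and covariates are often specified in an analysis plan that is not shown. That is fair: the text does not forbid adjustment. But it defines the contrast as a difference in means and describes plain resampling, and adjustment improves on that with data already planned. The possibility of a compatible reading does not remove the gain.

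Three stronger readings are tempting and are not supported.
- *Symptom effects are left unadjusted.* A reader might infer this, but the article states no between-arm model for symptoms. The only longitudinal model is "a repeated measurement of ANOVA, including all variables over time, will be performed to assess whether missing values respond to a random or non-random pattern", whose stated purpose is to examine missingness. There is no planned symptom estimator against which to measure a loss.
- *The economic results will be biased.* Over repeated randomisations the unadjusted differences are not biased by chance imbalance. It is part of sampling error, and resampling patients already carries it into the intervals. What is lost is efficiency, together with a point estimate shifted by whatever imbalance occurred.
- *The baseline tests will steer the analysis, or the gap could reverse the ratio.* No decision hangs on the tests as written, so they change no estimate. Whether a gap of this size could change the sign of the ratio depends on the true QALY gain, for which the article gives no value.

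**Conclusion.** The point holds in limited form. The baseline tests cannot do what they are said to do, and the cost and QALY contrasts are defined without baseline terms that are available. The consequence is avoidable random error.

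The size is illustrative only. At an assumed utility SD of 0.20 with half the gap persisting, one standard error of chance imbalance is worth about 0.012 QALY on the article's stated 12-month duration, or 0.017 to 0.020 over the treatment period plus follow-up. Over an assumed SD of 0.15 to 0.25 and both horizons the range is 0.009 to 0.024. The precision gain depends wholly on a correlation that the article does not give.

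**What to change.** - Replace the baseline significance tests with a descriptive table by arm, and reword the Allocation sentence so that randomisation is not said to guarantee comparable groups.
- Pre-specify the QALY difference adjusted for baseline EQ-5D utility and the cost difference adjusted for the 3-month pre-inclusion cost. Refit the regression in each bootstrap replicate and form the ratio from the adjusted differences. Seemingly unrelated regressions or separate linear models would both serve.
- State the time horizon over which QALYs and costs are accumulated, since the weight of baseline utility depends on it.
- When the between-arm model for the symptom scales is written, include the baseline score of the same scale. This is a recommendation for a model not yet stated.

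The cost is a few sentences of analysis text and slightly longer bootstrap code. No extra data collection is needed, provided that EQ-5D is administered at the baseline visit as the general schedule implies.
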